#### Sample size calculation

The effect of the intervention in the study by Shimazu et al. [17] corresponds to an odds ratio of 0.09 (IG: 8 vs. CG: 50 % relapses), equivalent to a Cohen’s d of 1.33, which can be considered as a very large effect. However, the sample size was comparatively small, consisting of only 57 patient-relative tandems. Furthermore, there are some major differences to our study. First, the intervention in our study will be conducted by different therapists at several study sites. Second, our study is closer to routine conditions. Therefore, our study population will be more heterogeneous than in the study by Shimazu et al. [17]. A sample size of 128 patient-relative tandems one year after discharge (T_4_) is sufficient to detect a moderate effect of Cohen’s d = 0.50 (Cohen’s f = 0.25) with a power of 80 % by analysing the primary outcome via ANCOVA. In the study by Shimazu et al. [17], the dropout rate was about 5 %. As our study will be conducted under routine conditions, we estimate a conservative dropout rate of 10 % (*N* = 18) for the time of the intervention and a further 20 % lost to follow-up (*N* = 32). To reach a sample size of 128 patients under consideration of a total dropout rate of 30 %, a total of 180 patient-relative tandems shall be randomised.

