### Measures taken to minimise/avoid bias

#### Randomisation and concealment of allocation

To control for known and unknown confounders and thus preclude selection bias, randomisation of patient-relative tandems will be conducted by means of a computer-based algorithm. Randomisation lists will adhere to a one-to-one study-group allocation ratio and will be stratified by centres with dynamically adaptable block sizes to prevent predictability and to ensure a balanced proportion of participants in both study conditions. To meet the challenges of a group intervention, randomisation blocks will include blocks with two, four, six, eight and ten patient-relative tandems. In each block size, the proportion of patient-relative tandems which will be allocated to the intervention or the control group is balanced. Once a study centre has recruited at least six patient-relative tandems, randomisation will be conducted with the appropriate block size. If a study centre has recruited two or four more patient-relative tandems before the first group session in the intervention group has taken place, they can be re-randomised and added to the PGIR and the control group. Randomisation lists will be centrally generated by the study statistician, who has no direct contact with clinicians or patient-relative tandems. To ensure allocation concealment, randomisation lists will be inaccessible to staff involved in the recruitment at the respective study centres. After recruitment of at least six patient-relative tandems (conducting the PGIR has to be feasible), study sites will report included patient-relative tandems to the leading study centre, which will report the allocation to the study sites as well as the patient-relative tandems. As the effect of the intervention was not moderated by any investigated variable in the study by Shimazu et al. [17], stratification for clinical characteristics will not be considered. However, central clinical variables (e.g., number of depressive episodes, duration of the current episode) will be gathered and their effects will be investigated in additional sensitivity analyses.

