### Statistical methods

#### Analyses

The primary outcome, i.e., estimated DFDs one year after discharge from inpatient depression treatment, will be analysed by means of an analysis of covariance (ANCOVA) (independent variables: intervention, study centre; dependent variable: DFDs; covariate: severity of depressive symptoms at baseline) comparing the number of DFDs one year after discharge from inpatient depression treatment between the intervention and the control group. The primary analysis will be performed according to the intention-to-treat principle including all randomised patients. Multiple imputations will be used to account for missing data. Analyses with an alternative method of dealing with missing data and using available data will only be performed as sensitivity analyses in order to test the robustness of the findings. Secondary interval-scaled outcomes will be tested using t-tests and analyses of covariance (ANCOVA, if baseline measurement of the outcome is available). Dichotomous outcomes will be analysed using Fisher’s exact test, chi-square test (depending on expected cell frequencies), or logistic regression (if covariates are present). To ensure the interpretability of the results, each inferential statistical analysis will be accompanied by descriptive analysis. Differences in time until rehospitalisation will be analysed using Cox regression. For parameters in which the variance cannot be calculated analytically (e.g., cost-effectiveness), bootstrap methods will be used. Longitudinal analyses will be performed using general (interval-scaled outcome) or generalised (binary or ordered categorical outcome) linear mixed models. For the primary confirmatory analysis, a result with a type-I error under 5 % (*p* < .05) will be considered as statistically significant. Every additional analysis is seen as exploratory. Accordingly, a correction of the type-I error inflation will not be applied.

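### The 30 % total dropout adds two rates with different denominators; the plan's own losses come to about 28 % and leave 130 tandems, which meets the required 128

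*Protocol article*

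**What the plan says.** All the figures are in the protocol article, under Sample size calculation.

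- Target: "A sample size of 128 patient-relative tandems one year after discharge" is described as "sufficient to detect a moderate effect of Cohen’s d = 0.50 (Cohen’s f = 0.25"), "with a power of 80 % by analysing the primary outcome via ANCOVA".
- First loss: "we estimate a conservative dropout rate of 10" %, given as 18 tandems, over the intervention period.
- Second loss: a further 20 % to follow-up, given as 32 tandems.
- Total: the step from 128 to the number randomised is made "under consideration of a total dropout rate of 30" %.
- Result: "a total of 180 patient-relative tandems shall be randomised".

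Two inputs come from other sections. Under Analyses: "For the primary confirmatory analysis, a result with a type-I error under 5" % counts as significant. Under Randomisation and concealment of allocation: "Randomisation lists will adhere to a one-to-one study-group allocation ratio". The Analyses section also plans an intention-to-treat analysis of every randomised patient, with multiple imputation for missing data.

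**The concern.** The section gives two head counts, a total rate, a target and a number randomised, and these do not all fit together. The head counts sum to 50 of 180, which is not 30 %. A 30 % loss from 180 does not leave 128, and the head counts do not leave exactly 128 either.

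The total rate is the figure that the text itself uses to go from 128 to 180. As written, a reader cannot tell whether the plan expects 130 or 126 tandems at twelve months. What is at stake is the accuracy of one figure in the sample size justification and the number of completers the plan can be taken to expect. The adequacy of 180 is not in doubt.

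**Working it through.** **Inputs.** From Sample size calculation: d = 0.50 (f = 0.25), power 80 %, 128 at twelve months, losses of 18 (10 %) and 32 (a further 20 %), total 30 %, 180 randomised. From Analyses: 5 % significance level. From Randomisation and concealment of allocation: 1:1 allocation. Assumption: a two-sided test, because the article does not state sidedness.

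**1. Reproduce the 128.** For two equal groups with N in total, the noncentrality parameter is d × √(N/4), and power comes from the noncentral t distribution with N − 2 degrees of freedom. At N = 128: 0.50 × √32 = 2.828, and power = 80.1 %. The plan's target is confirmed, which also supports the two-sided reading.

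**2. Find the denominator of the second loss.**
- 180 × 0.10 = 18, leaving 162.
- 20 % of 162 = 32.4, which rounds to the stated 32.
- 20 % of 180 = 36, which does not match.

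The second rate therefore applies to those left after the first loss.

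**3. Total loss on the plan's own counts.**
- 18 + 32 = 50, and 50/180 = 27.8 %.
- From the rates: 1 − 0.90 × 0.80 = 28.0 %.
- Remaining: 180 − 50 = 130, which is above 128.
- Number to randomise at 28 % loss: 128/0.72 = 177.8, so 178. The planned 180 covers this.

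**4. Total loss read literally as 30 %.**
- 180 × 0.70 = 126 remain, 2 below 128.
- Number to randomise: 128/0.70 = 182.9, so 183 (184 for equal arms).

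**5. Power for each count** (same formula as step 1).

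| Tandems at twelve months | Where the count comes from | Power |
|---|---|---|
| 126 | literal 30 % of 180 | 79.5 % |
| 128 | stated target | 80.1 % |
| 130 | listed losses of 18 and 32 | 80.8 % |

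Using N − 10 degrees of freedom, to allow for eight centres, the treatment effect and one covariate, lowers each figure by less than 0.1 percentage point.

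The 30 % is the plain sum 10 % + 20 %. It mixes a rate on 180 with a rate on 162.

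**The case against.** The strongest case against making anything of this is that 180 is sound. The head counts are explicit, can only come from sequential loss, and leave more than the target. Sequential loss needs 178, and even a literal 30 % needs only 183. This stands in full.

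A reader might nevertheless infer that the trial falls short of 128 and misses its 80 % power. The documents do not support that. The figure of 126 appears only if the wrongly summed 30 % overrides the plan's own counts. Even then, power of 79.5 % rounds to the 80 % stated. The calculation also takes no credit for baseline adjustment. If d = 0.50 is the unadjusted effect, which the article does not say, a correlation of about 0.12 between baseline severity and the outcome brings 126 tandems back to 80 %, and a correlation of 0.3 gives about 83 %. The primary analysis also includes all 180 through multiple imputation, although imputation does not fully restore lost information.

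A reader might also infer that retention would be judged against 30 % and a shortfall missed. Nothing in the article sets such a threshold or ties a decision to it. The explicit target at twelve months is 128.

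What the objection does not remove is the wrong figure. 27.8 % rounds to 28 %, not 30 %, and the 30 % stands in the sentence that justifies 180. Planning to impute does not settle it either, because the section bases its power on 128 tandems at twelve months.

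**Conclusion.** The point holds as a minor correction. The stated total dropout of 30 % contradicts the listed losses, which come to 50 of 180 (about 28 %) and leave 130 tandems with power of about 80.8 %. The required 128 is met and 180 needs no change. The gap between the two readings is 4 tandems (130 against 126) and about 1.2 percentage points of power (80.8 % against 79.5 %; 80.76 − 79.52 = 1.24 before rounding). No shortfall in sample size or power should be claimed.

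This rests on a two-sided 5 % test, equal arms, d = 0.50 with no gain from the covariate, and the reading that 32 is 20 % of 162. The plan's own numbers support that last reading.

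**What to change.** Correct one sentence under Sample size calculation. State the total dropout as about 28 % (18 of 180, then 32 of the remaining 162, so 50 of 180), with 130 tandems expected at twelve months against the 128 required, and keep 180 randomised.

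If 30 % is the intended planning rate, state instead that 126 tandems are expected, with power of about 79.5 %, and bring the two listed losses into line with that rate.

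The cost is one sentence. Enrolment, conduct and analysis do not change. Under the second option, the stated power becomes about half a percentage point less favourable than 80 %.

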## Discussion

Our study will provide information on the effects of PGIR as a maintenance treatment after inpatient depression treatment on central patient-related as well as relative-related outcomes, such as course of disease and social functioning in patients, as well as caregiver burden and expressed emotion in relatives. The PGIR approach evaluated within this trial faired very well in one small monocentre trial with a small sample size [17] but has never been evaluated within a multicentre trial. This is important, as small studies tend to overestimate effect sizes [21, 22]. The confirmation in a multisite study is therefore required. The brief intervention of our study is highly suitable for routine conditions regarding psychoeducation for relatives of patients in inpatient depression treatment [27]. The results of our study will be important, as they will close an evidence gap and can therefore clarify recommendations in current guidelines [5] and eventually foster the provision of PGIR as a sensible addition to depression treatment.

Potential limitations of our study include the fact that blinding of patients and relatives as well as therapists is not feasible. Furthermore, patients will differ widely regarding their clinical characteristics due to the broad inclusion criteria. Additionally, the group of relatives will be heterogeneous, as we are not focusing on a specific group of relatives, such as partners. Moreover, treatment and health care utilisation of patients and relatives will not be restricted. These aspects might dilute the effects of the intervention. However, this can also be seen as strength of our study, as the study population is likely to come close to routine conditions and hereby can ensure a high external validity of the results. A further limitation is that study participants have to self-administer a high number of measurement instruments. This might hinder the feasibility of the trial and reduce the response rate.

Relapse and rehospitalisations are major topics after inpatient depression treatment. PGIR is a highly promising approach to improve the course of disease in this burdensome disorder. However, high-quality studies dealing with PGIR as an additional intervention to stabilise outcomes after inpatient depression treatment are largely lacking.

## Trial status

Enrolment for the trial began in March 2015. At the time of manuscript submission, participants were still being recruited. Recruitment is expected to continue until March 2016. Data collection is expected to continue until March 2017.

## Abbreviations

ANCOVA: Analysis of covariance
CEA: Cost-effectiveness analysis
CSSRI-D: German version of the client sociodemographic and service receipt inventory
DEGS: German health interview and examination survey for adults
DFDs: Estimated number of depression-free-days
D-Lit: Depression literacy test
DRKS: German clinical trials register
FEF: Questionnaire on family atmosphere
FIMA: Questionnaire for health-related resource use
FQ: German version of the family questionnaire
ICD-10: International classification of disease, 10th revision
IEQ-EU: German version of the involvement evaluation questionnaire
IPQS-R: Scales for control attributions of the illness perception questionnaire for schizophrenia: relatives’ version
OSCE: Objective structured clinical examination
PCS: Perceived criticism scale
PHQ-9: 9-item version of the patient health questionnaire
PGIR: Psychoeducational group intervention for relatives
SCL-K-9: 9-item version of the symptom-ckecklist-90-R
SPSI-R-S: 25-item version of the social problem-solving inventory-revised
TAU: Treatment as usual
UTN: Universal trial number
WHODAS 2.0: WHO disability assessment schedule
